### Trial endpoints

The Primary Endpoint is the proportion of patients with at least one adjudicated probable or certain, non-trivial incident in-hospital ADR occurring within 14 days of enrollment during the index hospitalization.

### Secondary endpoints include

The proportion of patients with at least one adjudicated *possible, probable or certain*, non-trivial incident in-hospital ADR occurring within 14 days of enrollment during index hospitalization.The proportion of patients with at least one adjudicated probable or certain, non-trivial hospital-acquired, *pre-specified (as per* Table 2*) ADR* occurring within 14 days of enrollment during index hospitalization.The *number* of adjudicated probable or certain, non-trivial hospital-acquired ADRs occurring within 14 days of enrollment during the index hospitalization (i.e. the count of Primary Endpoint events).The *number of adjudicated possible, probable or certain*, non-trivial, incident, in-hospital ADR occurring within 14 days of enrollment during index hospitalization.The *number* of adjudicated probable or certain, non-trivial hospital-acquired, *pre-specified (as per* Table 2*)*, non-trivial, incident, in-hospital ADR occurring within 14 days of enrollment during index hospitalization.

**Table 2 Tab2:** Pre-specified event /ADR for which there is mandatory reporting of all events

Event	Definition
Fall/s	New fall/s
New onset unsteady gait	New onset of unsteady gait that results in poor mobility and unsteady balance
Acute kidney injury	An increase in serum creatinine by 0.3 mg/dl (26.5 μmol/l) within 48 h or an increase in serum creatinine by 1.5 baseline, which is known or presumed to have occurred within the prior 7 days
Symptomatic orthostatic hypotension	A systolic blood pressure drop ≥20 mmHg ± diastolic blood pressure drop ≥10 mmHg within 3 min of standing from the lying or sitting posture associated with symptoms
Major serum electrolyte disturbance	A sodium (Na) of < 130 mmol/l or > 145 mmol/l and/or a potassium (K+) < 3.5 mmol/l or > 5.2 mmol/l and/or a corrected calcium (Ca++) < 2.1 mmol/l or > 2.7 mmol/l
Symptomatic bradycardia	Heart rate of < 50 beats with symptoms
New major constipation	Subjective symptoms of hard stools and/or less than 3 bowel movements per week and/or supported by nursing records
Acute bleeding	Malaena or haematuria or haematemesis or haemoptysis with or without a drop in haemoglobin level > 2 g/dl (not due to rehydration) or associated symptoms (hypotension, tachycardia, pallor) or secondary renal failure
Acute dyspepsia/nausea/vomiting	Subjective symptoms of acute ‘indigestion’/‘upset stomach’ or acute abdominal pain or acute refusal to eat or acute heartburn/acid reflux or acute nausea/vomiting
Acute diarrhoea	New liquid stools reported by the patient or the nursing staff or new liquid stools detected by medical staff on physical examination or new liquid (non-solid) stools occurring more than 3 times in 24 h
Acute delirium	Confirmed by a reliable witness and the DSM-V criteria. Supported by a 4AT ≥ 4 and/or MMSE < 23/30
Symptomatic hypoglycaemia	Symptoms with a blood glucose of < 3.5 mmol/L or < 63 mg/dl.
Unspecified adverse event	For ADEs not specified above e.g. acute liver failure, anaphylaxis

Exploratory Endpoints include all-cause mortality during index hospitalization; re-hospitalisation, composite healthcare utilization, and health related quality of life at 12 weeks post-discharge follow-up; and utilization of non-pharmacological interventions.

### Patient safety

As the SENATOR Trial is not a regulated clinical trial and is not intended for marketing authorization, and in view of the proposed large recruitment of elderly multi-morbid subjects, full pharmacovigilance reporting of all adverse events will not be attempted. Clinicians are encouraged to report any ADRs in accordance with local clinical policies. Any protocol violation, participant injury consequent to study involvement or related to the application of SENATOR recommendations are reported by the site researchers using a standardized ‘Deleterious Event Form’ for review as appropriate by the Ethics Committee(s), Trial Coordinating Centre, Coordinating Investigator and the independent Ethics and Safety Review Group.

### Endpoint ascertainment

Potential ADRs are recorded by the site staff using dedicated primary endpoint assessment forms based on a retrospective review of all the available documentation within the medical record, including medical, nursing and allied health professional case note entries, laboratory values, radiology reports, electrocardiograms and other investigations. The eligible period for endpoint occurrence extends from the day of randomization to the time of index hospital discharge, or until 14 days post randomization, whichever occurs first. In those subjects whose discharge takes place after day 14 the medical record is further reviewed at the time of discharge to determine if any additional evidence from the subsequent hospital course is relevant to the aetiology of a potential study endpoint.

We identified the 12 most common types of ADRs which represent approximately 80% of all hospital-acquired ADRs in older multimorbid patients (Table 2). For each of these pre-specified types of event, we developed a separate primary endpoint event-specific form, based on a standard template as shown in Fig. 1, to allow for standardised ascertainment of data relevant to that type of event. Any other type of suspected ADRs is recorded using a generic primary endpoint adverse event form. As several medications may be implicated in the same event, the most likely culprit medication, if identifiable, and any other potentially causal or contributory medications implicated in the adverse event are recorded. Generic evidence that supports causality such as temporal relationship, dose response relationship, and response to re-challenge, are recorded, along with any additional qualifying explanatory text used by the local research staff. The unblinded Site Investigator records whether the ADR began prior to randomization (i.e. was prevalent and therefore not part of the primary endpoint) or occurred post-randomization, and his/her own assessment as to the probability of the event being an ADR, and the severity of the event. The strength of the available evidence supporting the event being an ADR is ascertained using the WHO-UMC ADR causality classification system [19], which categorizes ADRs as certain, probable, possible, unlikely or indeterminate. The severity of the event is classified using a modified Hartwig & Siegel scale [20], ranging from trivial (event requires no specific investigation or treatment and has no sequellae) to fatal.

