### ADR adjudication

The Potential Endpoint Form is sent electronically to the blinded members of the Potential Endpoint Adjudication Committee, consisting of the six clinical Site Principal Investigators. Each event is reviewed by up to five Potential Endpoint Adjudication Committee members, excluding members from the same site where the event occurred. Each reviewer independently assesses the likelihood of the event being medication-related and the severity of the event. An algorithm based on the concordance of the independent assessments determines the subsequent number of reviews required to obtain a final decision on whether a non-trivial ADR has occurred or not (Fig. 1). In brief, if the local site Principal Investigator, upon unblinded review of the patient’s case records and the Primary Endpoint Form, grades the event as either ‘unlikely’ or ‘certain’ and the Endpoint Liaison Officer concurs, then the Evidence Form is reviewed by a single blinded Endpoint Committee member (Stage 1). If the stage 1 Reviewer agrees with the Site Principal Investigator, this decision is accepted otherwise the form is reviewed by a second blinded Endpoint Committee member as per Stage 2 below.

All Potential Endpoints judged by the unblinded Site Principal Investigator to be possible, probable, or indeterminate ADRs are directly reviewed independently by two committee members who are blinded to the initial assessment (Stage 2). The adjudicated conclusion is determined by the Stage 2 Agreement Matrix (Fig. 2); where reviewers agree, or any disagreement is minor, an adjudicated result is assigned. For more substantive levels of disagreement, the review progresses to a 3rd blinded Endpoint Committee member (Stage 3) and a majority consensus prevails provided all 3 reviewers judge that the event is at least a possible ADR. Otherwise the event is adjudicated by consensus at a full committee meeting with the Site Principal Investigator being recused.

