We had initially proposed a cluster randomized trial adjusting for difference in baseline ADR risk using an ADR prediction tool such as the previously validated Gerontonet ADR Risk Scale [6]. This approach had the specific advantage of limiting contamination between the intervention and control arm, especially if it transpired that the same investigator was simultaneously attending a subject in both arms of the trial. However, in our feasibility study we discovered a very large degree of heterogeneity in ADR rates between different sites and between specialities within individual sites. Some of this heterogeneity may have resulted from initial limited standardization of our ADR reporting and adjudication processes and from sampling variability given the limited sizes of individual samples as well as real substantive differences between sites. Furthermore, we found that within our population the ADR predictions tools were inadequate for correcting for the between-cluster variability in baseline ADR risk. This made it impossible to exclude the possibility that any observed differences in the proposed trial might not simply be the consequence of an unequal distribution of baseline ADR risks across sites. We therefore adopted an individual level randomization, accepting that a degree of cross arm contamination might dilute the perceived effect size. However, even in a cluster design this effect is not fully prevented because junior medical staff routinely migrate between various specialities within a hospital and senior clinicians typically cross cover other specialist services at weekends and when working on-call outside of regular daytime hours.

The assessment of ADRs gives rise to several methodological complexities that have not previously been widely discussed in the literature. It is necessary to distinguish between prevalent (pre-dating the hospitalization and on occasion necessitating it) and incident ADRs, which occur during the index hospital stay. These are likely to differ in their characteristics, risk factors and consequences, making the distinction particularly relevant for ADR risk prediction tools. From the SENATOR trial viewpoint, it is necessary to exclude ADRs occurring prior to randomization; therefore outcomes in this trial will only include in-hospital incident ADRs that occur post randomization, but we also take account of whether identification and response to prevalent ADRs is influenced by study intervention.

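### Onset after randomization is part of the primary endpoint, but it is recorded by the unblinded site investigator and no blinded review of it is described

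*Protocol article*

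**What the plan says.** The section Trial endpoints defines the primary endpoint as the proportion of patients with "at least one adjudicated probable or certain, non-trivial incident in-hospital ADR occurring within 14 days of enrollment". An event must therefore pass three tests: causality, severity and onset. The Discussion confirms the third: "it is necessary to exclude ADRs occurring prior to randomization".

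The section Endpoint ascertainment gives the onset call to a person who knows the arm: "The unblinded Site Investigator records whether the ADR began prior to randomization (i.e. was prevalent and therefore not part of the primary endpoint". The same person also records "his/her own assessment as to the probability of the event being an ADR, and the severity of the event".

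The section ADR adjudication then describes the blinded step: "Each reviewer independently assesses the likelihood of the event being medication-related and the severity of the event". The algorithm ends in a "final decision on whether a non-trivial ADR has occurred or not". Onset is not named at any stage.

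On the start of the window, Endpoint ascertainment says: "The eligible period for endpoint occurrence extends from the day of randomization to the time of index hospital discharge". The same section separates prevalent from incident by randomization itself, and the endpoint definition counts from enrollment.

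**The concern.** The trial is open-label, and the section Report dissemination accepts that on-site researchers cannot be masked. Blinded assessment is therefore the main protection for a partly subjective outcome. Of the three items the site investigator records, two are described as re-judged blind. The third, onset, can by itself take an event out of the primary endpoint.

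The call is not always easy. Patients are acutely ill and may be randomized up to 60 h after arrival. Ascertainment is a retrospective chart review. The Discussion says that case records usually lack the timing detail needed to separate repeated occurrences. One form covers all occurrences of an event type, and the article does not say how onset is coded when a type occurs both before and after randomization.

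The authors recognise that open-label staff may submit events differentially. Their remedy is that every occurrence of 12 listed event types must be reported whatever its presumed cause. That governs whether a form is filed. It does not govern whether a filed event is then classed as prevalent. If that classification differs by arm, the primary odds ratio shifts directly.

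**Working it through.** **1. Who judges each element, as described**

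| Element of the endpoint | Site investigator (unblinded) | Blinded reviewers |
|---|---|---|
| Causality | recorded | assessed |
| Severity | recorded | assessed |
| Onset before or after randomization | recorded; prevalent means excluded | not mentioned |

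**2. The plan's own figure**

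Inputs from Sample size: control rate 18%, odds ratio 0.65, two-sided alpha 0.05, 900 per arm, 90% power.

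- Control odds: 0.18/0.82 = 0.2195. Intervention odds: 0.65 × 0.2195 = 0.1427, so p = 0.1427/1.1427 = 0.1249.
- Difference: 0.0551. Over 900 patients this is about 50 event patients.
- Power for two proportions (normal approximation, pooled variance under the null) is 90.3%; 892 per arm are needed for 90%. The plan's figure reproduces.

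**3. Sensitivity to differential onset classification**

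Assume no true effect, with 18% in both arms (162 event patients per arm). Let a fraction f of intervention-arm event patients be lost to a prevalent classification over and above any loss in control. The documents give no value for f; the values below are assumptions.

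The observed intervention rate is q = 0.18 × (1 − f). For f = 0.10:

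- q = 0.162; odds ratio = (0.162/0.838)/(0.18/0.82) = 0.88.
- Mean rate 0.171. Null standard error = √(2 × 0.171 × 0.829/900) = 0.01775; times 1.96 = 0.0348.
- Alternative standard error = √((0.18 × 0.82 + 0.162 × 0.838)/900) = 0.01774.
- Probability of a significant result favouring SENATOR = Φ((0.018 − 0.0348)/0.01774) = Φ(−0.946) = 17.2%. Adding the opposite tail gives 17.35%.

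| f (assumed) | Event patients lost | Observed rate | Odds ratio | Two-sided rejection probability |
|---|---|---|---|---|
| 5% | about 8 | 17.1% | 0.94 | 7.9% |
| 10% | about 16 | 16.2% | 0.88 | 17% |
| 20% | about 32 | 14.4% | 0.77 | 54% |

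The nominal value is 5%. To imitate the whole design effect, f would have to be 0.0551/0.18 = 30.6%, about 50 of 162 patients. If the true odds ratio were 0.65, f = 10% would move it to 0.58.

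**4. Classification that does not differ by arm**

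If both arms lost 10% of their event patients, the rates would be 16.2% and 11.2%, and power would fall from 90.3% to 86.5%. The null would not be distorted. The concern is therefore only with classification that depends on arm.

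These are unadjusted two-proportion calculations. The planned analysis is a logistic regression adjusted for site and admission type.

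**The case against.** Several points on the other side stand.

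- **Condensed text.** The article introduces the algorithm as a summary, the adjudication figure is not shown, and the endpoint is itself called adjudicated and incident. A reader might infer that onset is never adjudicated. The documents support only that no blinded review of onset is described.
- **Fate of prevalent-flagged forms.** A reader might infer that these forms are withheld from the committee. The article says only that such events fall outside the primary endpoint.
- **Evidence available to reviewers.** The form records temporal relationship and explanatory text, so reviewers may see timing. That helps, but no stated rule lets them overrule the site's onset call.
- **Baseline data.** Allocation is released only after the necessary baseline data are entered (Allocation concealment), and these include biochemistry, haematology, ECG and cognition (Data management). For electrolytes, renal function or delirium, prior status is documented before the arm is known. This narrows the room for differential flagging. It helps less for symptom-based types such as constipation or nausea.
- **Authors' awareness.** The Discussion says the trial will consider whether the intervention influences recognition of prevalent ADRs. No method is given, and the remark concedes that an arm effect is conceivable.
- **Start of the window.** Prevalent is defined by randomization in the same section, so the reference to the day is loose wording affecting same-day events, not a conflicting rule.

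A reader might also see a second unblinded gate in the route to adjudication, since at Stage 1 "If the stage 1 Reviewer agrees with the Site Principal Investigator, this decision is accepted". The documents do not support that. Closure there needs the Endpoint Liaison Officer's concurrence and an agreeing blinded reviewer from another site. What two reviewers would have decided instead depends on an agreement matrix that is not shown.

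**Conclusion.** The concern holds in limited form. A classification that decides membership of the primary endpoint is assigned to an unblinded person, the described blinded review does not cover it, and the mandatory-reporting safeguard does not reach it. This is a gap in the blinded-endpoint design as described. It is not evidence that bias occurred, and the documents do not establish its direction.

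On size, a differential net loss of about 16 of 162 event patients would raise the rejection probability under no effect from 5% to about 17%, with an odds ratio of 0.88. The 10% is an assumption, and it is a fraction of patients, not of events. The endpoint is at least one ADR, so a patient whose event is classed as prevalent still counts if another qualifying type remains. Reading 10% of flagged events as 10% of lost patients would therefore tend to overstate the effect.

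**What to change.** - Add onset, before or after the randomization time stamp, as a third item in the existing blinded review. Reviewers judge it from dated, arm-masked evidence without seeing the site's classification.
- Put forms that the site classes as prevalent through the same review.
- Use the time of randomization consistently as the start of the endpoint window, in place of the day of randomization and of enrollment.
- Tabulate prevalent classifications by arm.

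If the full protocol or adjudication charter already has blinded reviewers confirm onset, stating so would settle the main point.

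The cost is one extra field on a form the committee already reads, some additional form reviews, and revised adjudication wording. No new staff are needed, and the sample size, arms and primary model do not change.

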**Fig. 1 Fig1:**
[figure not shown]
Potential Endpoint Adjudication Process

While the recording of evidence supporting an ADR, in a blinded fashion, using the relevant Potential Endpoint Form facilitates the blinded assessment of possible ADRs by the Adjudication Committee, it does not in itself safeguard against the possibility of selective or differential reporting of events to the Adjudication Committee by local site staff. This is especially relevant in the context of an open label trial, as the decision to refer borderline events/possible ADRs is often highly subjective. To avoid against the incomplete or differential submission of potential endpoints according to study arm, we have mandated that all occurrences of the 12 pre-specified events as listed on Table 2 be reported regardless of their presumed aetiology. Compliance with this reporting approach is assessed by on-site monitoring.

Given the difficulty with objectively and reliably recording the number of separate discrete occurrences of a specific type of ADR (e.g. episodes of diarrhoea), especially when using retrospective data review, we have taken the approach of completing a single Potential Endpoint Form for each type of ADR. This summarizes the total available evidence that a particular drug played an etiological role in the genesis of part or the totality of the adverse event that may represent an ADR. Thus, only one form is completed for each type of event regardless of the number of possible discrete occurrences of that particular adverse event during the index hospitalization. A subject could experience several different types of ADRs which are each recorded on their specific case report form or on the generic Potential Endpoint Form, as appropriate.

### ADR adjudication

The Potential Endpoint Form is sent electronically to the blinded members of the Potential Endpoint Adjudication Committee, consisting of the six clinical Site Principal Investigators. Each event is reviewed by up to five Potential Endpoint Adjudication Committee members, excluding members from the same site where the event occurred. Each reviewer independently assesses the likelihood of the event being medication-related and the severity of the event. An algorithm based on the concordance of the independent assessments determines the subsequent number of reviews required to obtain a final decision on whether a non-trivial ADR has occurred or not (Fig. 1). In brief, if the local site Principal Investigator, upon unblinded review of the patient’s case records and the Primary Endpoint Form, grades the event as either ‘unlikely’ or ‘certain’ and the Endpoint Liaison Officer concurs, then the Evidence Form is reviewed by a single blinded Endpoint Committee member (Stage 1). If the stage 1 Reviewer agrees with the Site Principal Investigator, this decision is accepted otherwise the form is reviewed by a second blinded Endpoint Committee member as per Stage 2 below.

All Potential Endpoints judged by the unblinded Site Principal Investigator to be possible, probable, or indeterminate ADRs are directly reviewed independently by two committee members who are blinded to the initial assessment (Stage 2). The adjudicated conclusion is determined by the Stage 2 Agreement Matrix (Fig. 2); where reviewers agree, or any disagreement is minor, an adjudicated result is assigned. For more substantive levels of disagreement, the review progresses to a 3rd blinded Endpoint Committee member (Stage 3) and a majority consensus prevails provided all 3 reviewers judge that the event is at least a possible ADR. Otherwise the event is adjudicated by consensus at a full committee meeting with the Site Principal Investigator being recused.

